## Abstract

**Background:**

Chronic illnesses are the leading cause of morbidity and mortality and threaten the sustainability of healthcare systems worldwide. There is limited evidence in terms of the best modality and intensity of physical activity for improving cardiorespiratory capacity and quality of life in patients with chronic conditions. The objective of the EfiKroniK study is to estimate the common effect of innovative, individualized and supervised physical exercise, on cardiorespiratory functional capacity and quality of life across people with different chronic conditions.

**Methods/design:**

This is a multicentre clinical trial with a type I hybrid effectiveness-implementation design, including 370 patients each with one of four different chronic illnesses: solid cancer, blood cancer, chronic obstructive pulmonary disease or schizophrenia. Patients will be randomly divided into two parallel groups, stratified by illness type. Patients in both groups will receive a standard healthy life prescription (PVS, from the Spanish “*Prescribe Vida Saludable*”) and additionally, the EfiKroniK group will be prescribed a physical exercise programme tailored to each patient in terms of intensity in each session. The primary outcome variables will be cardiorespiratory functional capacity and quality of life. The secondary outcome variables will be signs and symptoms, psychological and social factors and specific laboratory parameters. We will also analyse the dose-response effect of the physical exercise programme. Qualitative variables will describe patients’ perception of the utility and suitability of the EfiKroniK programme, as well as their expectations and satisfaction, identifying barriers to and facilitators of the EfiKroniK implementation process through discussion groups. The study will be carried out on an intention-to-treat basis, comparing changes throughout the 1-year follow-up between groups, adjusting for baseline, by performing mixed-effect analysis of covariance. We will estimate the effect of time on repeated measures in each subject and changes in the EfiKroniK and PVS groups over time.

**Discussion:**

The study will provide the data necessary to allow us to prescribe physical exercise in a similar way to a drug and as a key part of the treatment of chronic illnesses within our healthcare system.

**Trial registration:**

NCT03810755.

**Date and version identifier:** October 9, 2020. Version2.0.

## Background

The prevalence of chronic illnesses is still growing and exceeds 80% among people above 65 years of age, accounting for at least 80% of consultations and 77% of expenditure in the public health system in the Basque Country [1, 2]. In particular, cardiovascular and respiratory diseases, cancer and diabetes, together with mental illnesses account for a high proportion of disease burden worldwide [3, 4]. The burden is due to their improved prognosis and creates a growing need to address health problems resulting from these conditions, their treatment and associated comorbidities [5–7]. The strategies proposed for addressing this threat to the sustainability of the health system include empowering patients in terms of health self-management, promotion of wellbeing and independence.

The promotion of healthy habits in healthcare settings has shown to be effective in the prevention and management of a large number of chronic conditions [8]. Specifically, physical activity has a key role to play in patients with cancer, schizophrenia or chronic obstructive pulmonary disease (COPD). These patients tend to be much less active due to limitations related to their illness [9–12].

The benefits of physical exercise are the result of improvements in cardiorespiratory functional capacity and quality and quantity of muscle mass. Specifically, the disruption of the body’s homeostasis caused by exercise activates anti-inflammatory mechanisms and strengthens the immune system, contributing to the fight against the development of tumours in patients with cancer, countering the chronic inflammatory state prevailing in metabolic syndrome associated with antipsychotic medications in patients with schizophrenia and increasing functional capacity in patients with COPD [10, 13, 14].

Let us imagine that everyone with chronic respiratory diseases, various types of cancer and mental illnesses would benefit from the effect of physical exercise [15–17]. How much might their quality of life and independence improve? To what extent might they experience reductions in symptoms, complications and relapses? Notably, more than half of patients with these conditions do not even receive advice on physical exercise from their doctors [18, 19], despite the fact that several clinical trials have shown good outcomes associated with physical exercise in the treatment of patients with chronic conditions [20].

This gap between knowledge and practice is due, on the one hand, to the fact that we still have limited knowledge regarding the therapeutic effects of exercise; in particular, most current data is based on the current generic guidelines regarding intensity, even though various studies have suggested that during exercise at the same relative intensity (for example, 80% of the maximum heart rate [HR]), the metabolic response varies markedly between individuals [21, 22]. In order to be able to prescribe physical activity as we do drugs, we need to know exactly what dose produces the most effective response with the lowest risk [10]. To this end, we must carry out proper monitoring and use widely accepted methods [23]. Specifically, to ensure safety and the stimulus desired, rather than using HR assessed by direct or indirect methods, it might be more accurate to tailor intensity recommendations based on lactate thresholds [24–26], as this approach is considered the gold standard for the individualised exercise prescriptions [27]. The variation in lactate accumulation allows us to assess the metabolic or energetic response of an individual to a given intensity, and determine metabolic thresholds, that is, specifically, aerobic and anaerobic thresholds. Lactate is a metabolite secreted to obtain energy from glucose and which can be re-used as a source of energy during exercise at moderate intensity. At higher levels of intensity, however, when the energy requirements are greater than the capacity of the body to reuse generated lactate, this metabolite starts to accumulate [28]. Further, lactate accumulation is an indicator of a large number of processes occurring in the body as a result of exercise and which are good for the health.

On the other hand, numerous difficulties are encountered in translating the knowledge available to routine clinical practice [29] in health systems that are more focused on treating the pathological aspects of illnesses than in strengthening the health of individuals with these illnesses. In all sectors, growing importance is being placed on integrating the promotion of physical activity into the treatment of individuals with chronic conditions [9, 18, 30] but it remains unclear how to do this in an effective, widespread and sustainable way.

The clinical intervention assessed in EfiKroniK is physical exercise, which has an impact on the pathophysiological mechanisms underlying the aforementioned chronic conditions and facilitates the adaptive response of individuals to the limitations imposed by their condition, improving health-related quality of life, functional capacity and independence [12, 31, 32]. A review being carried out by Nunan and colleagues will strengthen the quality of the evidence regarding exercise as a medicine and will develop a taxonomy for prescribing physical activity [33]. That said, the data currently available, especially for the advanced stages of illness on which EfiKroniK is to focus, are often based on small observational studies that are vulnerable to potential confounders. Further, we have limited knowledge concerning the best modality and intensity of exercise, as well as the minimum therapeutic dose, and its effect at the individual level, to help us identify which patients might most benefit from exercise prescription [11, 32]. All this information is necessary to be able to prescribe physical exercise in a similar way to a drug [3].

## Clinical objectives

The objectives are:

To estimate the common effect of the innovative EfiKroniK programme of physical exercise, supervised by fitness and health professionals, across people with various different chronic conditions (solid or blood cancer, COPD or schizophrenia), compared to that of a general intervention promoting healthy habits (physical activity, balanced diet and smoking cessation). The effectiveness will be explored in terms of:
Cardiorespiratory functional capacity estimated using a 400-m walk testQuality of life and utility, measured using generic and specific questionnaires for each conditionSymptoms, and psychological and social well-being.

*All of these variables will be assessed on recruitment and at 3, 6 and 12 months of follow-up.

We will also measure specific blood parameters at baseline and 3 months (adiponectin, C-reactive protein, TNF-α, Il-1, Il-6, brain-derived neurotrophic factor [BDNF]).

To assess the dose-response relationship between exercise performed and the aforementioned response variables, as well as the predictive, moderating and mediating role of each illness, its treatment and patient characteristics, to build a predictive model of the clinical outcomes of the programme based on these clinical variables.

To estimate the associated costs for the EfiKroniK group and the standard healthy lifestyle prescription (hereon PVS, from the Spanish “*Prescribe Vida Saludable*” meaning prescribing a healthy lifestyle) group and calculate incremental cost-effectiveness and cost-utility ratios.

### Implementation objectives

To describe patients’ perception of the usefulness and appropriateness of the EfiKroniK programme, as well as their expectations and satisfaction.To identify barriers to and facilitators of the widespread, sustainable and ongoing implementation of EfiKroniK, as well as the adherence of patients, to guide the design of future strategies for implementing and rolling out this programme which will be assessed in future implementation trials.

## Methodology

### Study design

This will be a multicentre pragmatic open-label type I hybrid implementation-effectiveness trial, in which a total of 370 patients each with one of 4 different chronic conditions, namely, solid cancer (*n* = 100) and blood cancers (*n* = 70), COPD (n = 100) or schizophrenia (n = 100), will be randomised to one of two parallel groups, stratified by illness type: the EfiKroniK group (EG) (tailored exercise supervised by fitness and health professionals) or the reference group (PVS group) [34]. We deliberately opted to study diverse illnesses seeking to demonstrate any common effect of physical exercise across all of them, independent of any additional effects on each condition separately, and for this purpose, this design is much more efficient than separate clinical trials for each illness. Cardiorespiratory functional capacity at 3, 6 and 12 months and quality of life at baseline and at 6 and 12 months will be considered the primary outcome variables, and we will compare changes over time in both groups. Additionally, we will explore the perceptions of participants and professionals in terms of the feasibility of the programme, as well as the barriers and facilitators for adherence and continuity.

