### Outcome measures

These measurements are made by an interviewer blind to group allocation.

*Primary outcome measure* (baseline, 3, 6 and 12 months):
Cardiorespiratory functional capacity, as assessed using a 400-m walk testChanges in health-related quality of life, as assessed using the 36-item Short-Form Health Survey (SF-36) and disease-specific questionnaires: the European Organization for the Research and Treatment of Cancer Quality of Life Questionnaire (EORTC QLQ-C30) in patients with cancer; and the COPD Assessment Test (CAT) and Chronic Respiratory Disease Questionnaire (CRQ) in patients with COPD.

*Secondary outcome measures* (baseline, 3, 6 and 12 months):
Muscle strength test measured by the handgrip strength and sit-and-stand testsThresholds for lactate (LT1 and MLSS), HR, and accelerometer activity counts for tailoring the exercises, determined in submaximal walking or running tests. For detecting LT1, a test will be carried out on a 20-m track. This will be an incremental test combining 2-min active period and 1-min rest period. To help the participant adjust their speed in each 2-min period, red markers will be placed every 5 m on the floor and the wall on both sides and two large cones on the floor at each end of the track. Participants will be asked to reach the next red markers each time they hear a beep, continually adjusting their speed but without stopping; that is, they should go faster or more slowly seeking to pass each set of markers at the time of the corresponding beep. The speed will start at 2.4 km/h in the first stage; and will increase by 0.61 km/h each stage [40]. At the end of each stage, the following will be recorded: HR, Rating of Perceived Exertion and lactate concentration, by taking a blood sample from each earlobe to find the minimum lactate equivalent (LEmin) above which the lactate concentration starts to increase exponentially. Hence, the aerobic threshold is defined as the intensity of exercise (speed) at which the lowest recorded lactate level is followed by changes ≥0.1 mmol/L in the next stage and > 0.2 mmol/L the one after [25]. The test will be stopped if the participant becomes exhausted or lactate levels exceed 3 mmol/L.

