### Sample size

We expect to recruit a total of 370 patients over 2 years; with a loss to follow-up (including deaths) of 30%, this would provide the study with a power of over 90% to detect differences between the two comparison groups in the primary outcome variable (400-m walk completion time) of at least 6 s after 3 months, 12 s after 6 months and 24 s after 12 months of follow-up as significant (alpha = 0.05), assuming a linear increase in the impact of the exercise over time, a standard deviation of 40 s and intra-patient correlation of 0.6. These differences are less than those found in previous studies.

Regarding the quality of life outcome variable, we would have a power of 90% to detect differences between the two groups of 2.5 points at 3 months, 5 points at 6 months and 10 points at 12 months as significant (alpha = 0.05), for all the dimensions of the SF-36 questionnaire, except for physical and emotional roles (80% power) [40].

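### The protocol names two primary outcomes, then one, then a quality-of-life battery with no chosen score, and gives each test alpha 0.05; the quality-of-life visits also conflict.

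*Protocol article*

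**What the plan says.** **Number of primary outcomes.** The Abstract (Methods/design) names two: "The primary outcome variables will be cardiorespiratory functional capacity and quality of life". Study design repeats both. Sample size uses the singular when it states the power to detect differences "in the primary outcome variable (400-m walk completion time").

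**Content of the second outcome.** Outcome measures lists under its primary heading "health-related quality of life, as assessed using the 36-item Short-Form Health Survey (SF-36) and disease-specific questionnaires". These are the EORTC QLQ-C30 for cancer, and the CAT and CRQ for COPD. No scale, dimension or summary score is singled out.

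**Significance level.** Sample size uses alpha 0.05 for the walk. It uses 0.05 again for quality of life, with 90% power "for all the dimensions of the SF-36 questionnaire, except for physical and emotional roles (80% power"). Statistical analysis tests the group-by-time interaction at p < 0.05. The only stricter threshold, 0.005, is for subgroup interactions. No order of testing, division of alpha or joint-success rule is given.

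**Quality-of-life visits.** Study design has "quality of life at baseline and at 6 and 12 months will be considered the primary outcome variables", with no 3-month visit. The primary list in Outcome measures is headed "baseline, 3, 6 and 12 months". Clinical objectives also includes 3 months, and Sample size powers "differences between the two groups of 2.5 points at 3 months, 5 points at 6 months and 10 points at 12 months".

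**The concern.** A reader cannot tell whether the trial has one primary test, two, or about a dozen. That matters because 0.05 is set for each test. With several tests called primary and no success rule, a result on any one scale could be presented as a positive primary result, at an error rate above 0.05.

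The disease-specific questionnaires raise a further difficulty. The stated aim is an effect common to all four illnesses, but these instruments exist only for part of the sample, so they cannot be primary evidence for that aim.

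The visit conflict is a separate matter. It leaves unclear whether quality of life at the end of the supervised phase is a primary measurement, although the power statement assumes a difference at that visit.

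**Working it through.** **1. The plan's own walk figure.** Inputs from Sample size: 370 patients, 30% loss, SD 40 s, intra-patient correlation 0.6, differences of 6, 12 and 24 s at 3, 6 and 12 months, alpha 0.05 (taken as two-sided). Allocation is 1:1 (Randomisation).
- Evaluable per arm: 370 × 0.7 / 2 = 129.5.
- Slope difference: 6/3 = 12/6 = 24/12 = 2 s per month.
- Visits 0, 3, 6, 12 have mean 5.25, so Sxx = 27.56 + 5.06 + 0.56 + 45.56 = 78.75.
- Under compound symmetry, SE = √[2 × 40² × (1 − 0.6) / (78.75 × 129.5)] = 0.354.
- Power = Φ(2/0.354 − 1.960) = Φ(3.69) ≈ 99.99%.

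The stated figure of over 90% is reproduced as a lower bound for the group-by-time test. The quality-of-life power cannot be checked, because no SF-36 standard deviation is given. The stated 90% and 80% are used as they stand.

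**2. Error rate if success on any primary test counts.** For k independent tests it is 1 − 0.95^k. For tests with common correlation ρ and c = 1.960, it is 1 − ∫[Φ((c − √ρ·x)/√(1−ρ)) − Φ((−c − √ρ·x)/√(1−ρ))]^k φ(x) dx.

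| Tests | ρ = 0 | ρ = 0.5 | ρ = 0.8 |
|---|---|---|---|
| 2 (walk, one quality-of-life score) | 9.75% | 9.1% | 7.8% |
| 9 (walk, eight SF-36 dimensions) | 37.0% | 26.9% | 16.6% |

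The count of eight and the correlations are assumptions; the protocol gives neither. The disease-specific scales are not counted.

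**3. If every primary test must succeed.** Type I error does not exceed 0.05.
- Walk plus one SF-36 dimension: if independent, 0.9999 × 0.90 ≈ 90%, or 0.9999 × 0.80 ≈ 80% for a role dimension.
- Walk plus all eight (six at 90%, two at 80%): at most 80%. If independent, 0.9999 × 0.90⁶ × 0.80² ≈ 34%.

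**4. If alpha is split equally between two outcomes (0.025 each).**
- Walk: Φ(5.645 − 2.241) > 99.9%.
- Quality of life stated at 90%: Φ(1.960 + 1.282 − 2.241) = Φ(1.00) ≈ 84%.
- Quality of life stated at 80%: Φ(1.960 + 0.842 − 2.241) = Φ(0.56) ≈ 71%.

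**5. Coverage of the disease-specific scales (Study design numbers).** EORTC QLQ-C30: 100 + 70 = 170 of 370 (46%). CAT and CRQ: 100 of 370 (27%). No disease-specific quality-of-life questionnaire is listed for the 100 patients with schizophrenia.

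**6. Visits side by side.** Clinical objectives, Outcome measures and Sample size all include quality of life at 3 months. Study design does not.

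**The case against.** **The rule may be in an analysis plan that is not shown.** This is fair, and the absence of a multiplicity rule is not itself the point. What stands is what this document fixes. It counts the primary outcomes inconsistently, chooses no quality-of-life score, and bases its sample size on 0.05 for the walk and 0.05 for every SF-36 dimension. A later alpha split would not deliver the stated quality-of-life power (step 4).

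**A reader might take 37%, or any figure in the table, as the trial's error rate.** The document does not support that. It never says that one positive scale makes the trial positive. The figures hold only under that reading, and the larger ones also need the assumed eight dimensions and low correlation. For the walk alone, little changes, since its power survives an alpha split.

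**A reader might add that three follow-up visits multiply the tests further.** They do not, on this text. Statistical analysis describes one group-by-time test per outcome, followed by visit-specific estimates with confidence intervals. The visit conflict likewise has no bearing on alpha.

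**A reader might infer that 3-month quality-of-life data will be lost.** That is unlikely. Study design is a summary, and read literally it omits the baseline walk too. The operative outcome list includes 3 months, and Quality control refers to fieldwork manuals.

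**The disease-specific scales have a purpose of their own.** Study design does separate the common effect from effects specific to each condition. That supports measuring them, but not listing them as primary.

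**Conclusion.** The point holds in a conditional form. The primary outcome is described in ways that cannot all be true, and 0.05 is a per-test level. If any primary success counts, and the document states no other rule, the error rate is about 8–10% for two outcomes. For the walk plus eight SF-36 dimensions it is about 17–37%, assuming eight dimensions and correlations from 0 to 0.8. If all must succeed, alpha is held and power is what suffers: hardly at all with one quality-of-life score at 90%, but to 80% or below across all eight dimensions.

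The quality-of-life visit conflict is real and separate. It is an inconsistency to reconcile and does not contribute to the error rate.

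**What to change.** **Primary testing.** State the 400-m walk as the first primary test at 0.05, which matches Sample size. Then test one pre-named SF-36 score at 0.05, only if the walk test succeeds. State the power for that score with its standard deviation.

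**Acceptable alternative.** Keep two primary outcomes, name the single quality-of-life score, and state either an alpha split or a both-must-succeed rule, with power restated for the rule chosen. An equal split takes the quality-of-life power to about 84% or 71%.

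**Other scales.** List the remaining SF-36 dimensions, EORTC QLQ-C30, CAT and CRQ as secondary, and make the Abstract, Study design, Outcome measures and Sample size agree.

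**Visits.** Add 3 months to the quality-of-life schedule in Study design, in line with Clinical objectives, Outcome measures and Sample size.

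**Cost.** No extra patients are needed, and under the fixed sequence the walk test keeps its full alpha. But this is more than a wording change. Single dimensions lose primary status, and under the fixed sequence quality of life is confirmatory only if the walk test succeeds. Because this changes what a registered trial can claim, it should be made as a documented amendment.

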### Study population

#### Inclusion criteria

Participants are required to be between 18 and 75 years old and diagnosed with: stage IV solid cancer specifically colon, breast or non-small-cell lung cancer, have an Eastern Cooperative Oncology Group ECOG Performance Status of ≤1, and be on standard first-line chemotherapy; malignant blood cancer and have received an autologous transplant or non-localised lymphoma and be on immune therapy; schizophrenia including first-episode psychosis or other psychotic disorders; or clinically stable (no exacerbation, antibiotic treatment, systemic corticosteroid therapy or hospitalization in the previous 30 days) COPD with a BODE index of 3–7 and a life expectancy > 2 years. In addition, the following are required for patients to be eligible for inclusion: good renal, liver and blood function, with haemoglobin levels > 10 g/dl, a platelet count > 50,000, neutrophil count > 1000, and Karnofsky Performance Status score > 60, and an Eastern Cooperative Oncology Group Performance Status score ≥ 1.

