#### Exclusion criteria

Patients are to be excluded if they have brain metastasis, high risk of fracture due to bone metastasis, severe emotional instability, cardiorespiratory compromise or uncontrolled infection; relapse or progression of blood cancer; alterations in communication or significant cognitive impairment that might hinder data collection; bronchiectasis or lung disease other than COPD; other comorbidities that might hinder or prevent them from following the exercise programme; or uncontrolled high blood pressure (systolic > 200 or diastolic > 110 mmHg).

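### The inclusion criteria set two ECOG limits in opposite directions: read literally, solid-cancer patients qualify only at ECOG 1 and ECOG 0 is ineligible in all four illness groups

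*Protocol article*

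**What the plan says.** Both limits stand in one paragraph of the protocol article, under Study population, Inclusion criteria.

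- The solid-cancer clause requires patients to "have an Eastern Cooperative Oncology Group ECOG Performance Status of ≤1, and be on standard first-line chemotherapy".
- After the illness-specific clauses, a general sentence opens with "In addition, the following are required for patients to be eligible for inclusion". It lists good renal, liver and blood function, thresholds for haemoglobin, platelets and neutrophils, and "Karnofsky Performance Status score > 60". It ends: "and an Eastern Cooperative Oncology Group Performance Status score ≥ 1".

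The general sentence is not restricted to any illness. The clauses for blood cancer, COPD and schizophrenia contain no ECOG limit of their own. The Exclusion criteria do not mention ECOG, and no other section restates or corrects either limit. Study design plans 100 patients with solid cancer, 70 with blood cancer, 100 with COPD and 100 with schizophrenia.

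**The concern.** Two limits on the same scale, pointing opposite ways, apply cumulatively to the same patients. The first admits ECOG 0 in solid cancer and the second shuts it out. The second also sits oddly in its own list, where every other item sets a minimum of health and it alone sets a minimum of impairment.

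What is at stake is the definition of the trial population. Under Recruitment, patients are identified by oncology, haematology and pulmonology services, primary care doctors and the mental health network. A screener applying the sentence as written and one taking it for a slip would reach different decisions about the same ECOG 0 patient. A reader of the results could not tell from this text whether such patients were meant to be represented.

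**Working it through.** There is no stated figure to reproduce. The check is the intersection of the written conditions, taking ECOG in its usual orientation (0 is the best function, higher is worse), which the article does not spell out.

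**Inputs (Inclusion criteria; group sizes from Study design)**

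- A: solid-cancer clause, ECOG ≤ 1, so {0, 1}.
- B: general clause, ECOG ≥ 1, no upper limit stated, all illnesses.
- Link: B applies in addition to the illness-specific clause, so the conditions combine as AND.

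**Result by group**

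| Group | Planned n | ECOG conditions | ECOG values admitted |
|---|---|---|---|
| Solid cancer | 100 | A and B | {0, 1} ∩ {1 or higher} = {1} |
| Blood cancer | 70 | B only | 1 or higher |
| COPD | 100 | B only | 1 or higher |
| Schizophrenia | 100 | B only | 1 or higher |

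ECOG 0 appears in no row. The clause therefore covers 100 + 70 + 100 + 100 = 370 planned patients. For 70 + 100 + 100 = 270 of them, no upper ECOG limit is stated.

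**Direction of each item in the general list**

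| Item | Whom it removes |
|---|---|
| Good renal, liver and blood function | the less healthy |
| Haemoglobin > 10 g/dl | the less healthy |
| Platelets > 50,000 | the less healthy |
| Neutrophils > 1000 | the less healthy |
| Karnofsky > 60 | the less functional |
| ECOG ≥ 1 | the most functional |

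The last two rows both measure performance status and cut at opposite ends.

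**What cannot be computed.** The number of candidates whose eligibility changes is the number at ECOG 0 who meet every other criterion. The article gives no ECOG distribution for any group, so neither that number nor any effect on recruitment can be derived.

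**The case against.** The strongest defence is that this is a misprint with limited consequences. The clauses are not mutually exclusive, because ECOG 1 meets both. The direction of the neighbouring items points to a reversed sign. Sites may work from the full protocol and the fieldwork manuals mentioned under Quality control, none of which is shown. This stands in part: divergent screening between sites is a possibility, not something the article demonstrates. It does not remove the conflict, which is stated in the eligibility text itself and is not a detail left to a fuller document.

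A second defence is that a floor on impairment was intended, since the Background says the trial focuses on advanced stages of illness. That cannot be ruled out. It does sit badly beside a solid-cancer limit that expressly admits ECOG 0, and no rationale for a floor is given. For the same reason, the article does not establish that the sign is wrong.

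Several stronger readings are tempting and are not supported:

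- *The solid-cancer group is emptied.* It is narrowed to one value.
- *The treatment comparison is biased.* Randomisation is central, 1:1 and stratified by illness, and follows eligibility. Inconsistent ECOG screening would change the population, not favour an arm.
- *Recruitment towards 370 is compromised.* Without an ECOG distribution this is conjecture. The 370 counts patients the clause covers, not patients it would turn away.
- *Unfit patients are let into an exercise programme.* Barring ECOG 0 adds no such risk. At the impaired end, Karnofsky above 60 applies to everyone, the Exclusion criteria remove cardiorespiratory compromise and comorbidities that would prevent participation, and COPD has its own BODE range of 3–7. The missing ECOG ceiling in three groups is not shown to be a defect.

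**Conclusion.** The point holds as an internal contradiction in an operative eligibility rule. As written, solid-cancer patients are eligible only at ECOG 1, and ECOG 0 patients are ineligible in all four illness groups. The conclusion rests on the literal text, on the general clause being cumulative and unrestricted by illness, and on the usual orientation of the scale.

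The consequence is for who is enrolled and how far the results generalise; the validity of the randomised comparison is untouched. The number of patients affected is unknown. Which limit was intended is for the sponsor to say; the document does not settle it.

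**What to change.** The sponsor should reconcile the two clauses and state, for each of the four illness groups, whether an ECOG limit applies, what it is and in which direction it runs, checked for consistency with the Karnofsky criterion. If a floor is intended, the text should say so and give the reason, and the solid-cancer clause should be reworded to agree with it.

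The article does not report recruitment status. If screening has started, sites should be notified and the screening records checked to see which limit was applied, so that the enrolled population can be described accurately.

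The textual correction is small. The record check, if needed, costs more, depending on how many patients have been screened. Neither touches the sample size or the analysis.
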